## Abstract

**Introduction:**

Lennox–Gastaut Syndrome (LGS) is a severe developmental epileptic encephalopathy without a known cure. Management of symptoms requires substantial care. Treatment options include anti-seizure medications, dietary therapy, and epilepsy surgery. Two main treatment pathways for patients with LGS with drug resistant epilepsy are additional anti-seizure medications or epilepsy surgery, which have been reported to be effective in reduction of seizure burden and improving quality of life. No studies have directly compared the outcomes of using epilepsy surgery versus using additional anti-seizure medications for the treatment of LGS.

**Methods:**

This study is a multicenter, mixed-methods comparative effectiveness study of LGS patients who have undergone epilepsy surgery or have received an LGS-approved medication for treatment resistant seizures. Aim 1 will analyze the effect of surgical therapies and additional medication on two clinical outcomes: (1a) seizure-related healthcare utilization, and (1b) expressive communication, behavior, and parent-reported quality of life. Based on electronic health record review and coding validation as part of Aim 1a, we will develop computable phenotypes for LGS. The phenotypes will inform the analyses in Aim 1a and Aim 2. Aim 2 will describe the real-world utilization of these treatments across multiple healthcare institutions in the United States. Data will be collected from electronic health records, data marts in the National Patient-Centered Clinical Research Network (PCORnet®) format, caregiver surveys, and focus groups.

**Discussion:**

This study of LGS will provide currently unavailable evidence concerning the real-world comparative effectiveness of epilepsy surgeries and additional anti-seizure medications. The outcomes are those that families identify as important: emergency medical care for seizures and patients’ functional outcomes. The results of this study may help guide decisions regarding the treatment of LGS and development of computable phenotypes for this rare disease. This study using PCORnet® data will also lay the groundwork for future large-scale studies on LGS and other rare epilepsies.

**Clinical trial registration:**

ClinicalTrials.gov, identifier NCT05374824.

## Introduction

1

Lennox–Gastaut Syndrome (LGS) is a severe developmental epileptic encephalopathy that affects an estimated 48,000 children and adults in the United States (US) (1). LGS is characterized by multiple seizure types, life-long treatment resistant seizures, developmental delay, cognitive and behavioral impairments, and early death (2–4). The onset of seizures is typically in the first 2 years of life, but the syndrome is often not fully recognizable until children are 3 to 5 years old (2, 5). Individuals with LGS have multiple types of seizures including tonic–clonic, tonic, and atonic seizures (2). Prolonged seizures are common and require the use of rescue medications, emergency department (ED) visits, and unplanned hospital admissions (6, 7).

LGS, although rare, accounts for a disproportionate amount of healthcare utilization and expenditures. It accounts for up to 10% of all childhood-onset epilepsies and 1–2% of all epilepsies; however, it represents one-fifth or more of treatment resistant pediatric epilepsy (2, 8–10). Among children and adults, expenditures are two or more times greater in association with LGS than with other forms of epilepsy (11), and all-cause mortality in young people with LGS is ten times that in the general population (3). In a survey about living with LGS, 75% of parents reported that their child experienced seizures every day in the prior week, 30% reported going to an ED at least once in the past 6 months, and 51% reported using rescue medication to stop a seizure in the past 6 months (7). In addition to the burdens created by seizures, people with LGS have a profound level of cognitive and physical impairment. A caregiver-driven survey of young people with severe epilepsies found that in the subgroup with LGS, 42% did not walk independently, 25% did not have functional hand grasp, 42% were entirely dependent on someone else for feeding, 55% did not effectively communicate, and 50% were nonverbal (4). This degree of impairment further increases medical burden and financial stress with hidden costs of care, and significantly impacts the quality of life of patients with LGS and their families (12, 13).

Currently, no cure for LGS exists, and available treatments for LGS are directed at symptom management (6, 14). Treatment options include anti-seizure medications, dietary therapy, and epilepsy surgery. The two primary therapy pathways are surgical approaches, which include Vagus nerve stimulation (VNS), other forms of neurostimulation, and corpus callosotomy (CC), and anti-seizure medications approved for the treatment of LGS. There is a significant gap in current evidence regarding the recommended treatment journey for patients with LGS who experience many seizures each week and have not responded to multiple medications. Each therapeutic approach has been found to have a moderate impact on seizure frequency (15–19). Apart from a small, nonrandomized retrospective study of VNS versus CC (20), none of the approaches have been directly compared to determine which is more effective. Currently, decisions about which treatment strategies to employ rely on studies with significant heterogeneity in their study populations and in their outcome measures (17, 18). In the case of surgery, evidence rests mostly on uncontrolled retrospective and prospective series showing before-and-after comparisons and partly on clinical trials with limited representativeness and generalizability (15, 20–24). Few studies have investigated whether epilepsy surgery or another medication will improve a child’s cognitive and functional profile. A study of 16 patients with “LGS-like” epilepsy suggested improvements in cognition and behavior 6 months after Vagus nerve stimulator implantation (25).

Parents making treatment decisions for a child with LGS face frightening and potentially dangerous options. Baca et al. highlighted the emotional and informational hurdles parents must overcome before deciding to pursue surgery (26). The decision to add medication or to undergo surgery is not simple. Parents and providers question whether surgery – with its associated preparations, stress, intraoperative risks, and risks of post-surgical complications – outweighs the benefits of adding medication. Adding medication is also not simple, because these medications are associated with significant, even dangerous adverse effects individually and in combination. At least one of the medications specifically approved for LGS, felbamate, received a black box warning shortly after its approval in 1993 because of the risk of severe aplastic anemia and hepatic failure (27). All six of the other FDA-approved medications for LGS (clobazam, lamotrigine, topiramate, rufinamide, fenfluramine, and cannabidiol) can have significant adverse effects (18).

Delaying effective treatment may expose the child to longer periods of uncontrolled seizures, leading to greater decline and long-term disability. Early intervention may limit the impact of seizures in the young brain and may result in less impairment later in life (28–34). A comparative effectiveness study is needed to support informed decisions in the management of this challenging disease. A study comparing surgical procedures versus the addition of LGS-approved medication may help guide future decision-making regarding the treatment journey of LGS and may improve patient outcomes.

## Methods and analysis

2

### Study aims

2.1

Aim 1: Determine the effect of epilepsy surgery and LGS-approved anti-seizure medications on two key clinical outcomes in children with LGS.

a. Compare the effectiveness of the addition of surgeries versus the addition of another medication for reducing seizure-related emergency healthcare utilization.

b. Compare the effectiveness of these two pathways and of early versus later use of surgery versus medications on measures of children’s expressive communication, behavior, and quality of life.

Aim 2: For individuals with LGS, describe real-world utilization of these treatments across multiple centers in the US, and identify variability including disparities that may currently pose challenges and barriers to ensuring optimum access to and use of appropriate therapies.

### Study design

2.2

This multicenter, mixed-methods comparative effectiveness study will use the Patient-Centered Clinical Research Network (PCORnet®) data mart infrastructure to work with 18 academic pediatric sites across 5 clinical research networks: PEDSnet, a national pediatric learning health system; PaTH Towards a Learning Health System (PaTH); Stakeholders, Technology, and Research (STAR); OneFlorida+; and Greater Plains Collaborative. PCORnet® is a national research network of health systems with access to electronic health records (EHR) data that have been standardized using a common data model (35). The 18 PCORnet® sites we selected have large clinical programs in pediatric epilepsy and serve large numbers of patients with LGS. At 7 high-intensity sites, clinical research teams will conduct EHR review for coding validation of the diagnosis of LGS and will recruit caregivers to complete surveys measuring communication, behavior, and quality of life. Computable phenotypes for LGS will be developed based on elements available in the EHR. Data from an additional 11 sites (light-touch sites) will be pulled and analyzed based on cohort identification by these computable phenotypes (Figure 1).

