#### Aim 1a

2.2.1

Through a retrospective chart review study across the 7 high-intensity sites, we will validate the International Classification of Diseases, Tenth Revision (ICD-10) codes for LGS and will develop computable phenotypes for LGS.

In a retrospective cohort study across the 7 high-intensity sites, we will compare the effectiveness of epilepsy surgery versus additional medication for decreasing seizure-related ED visits and inpatient admissions in patients with validated diagnoses of LGS. This will entail a comparison of any surgery versus the medication arm, as well as comparisons of each of the two most common surgical approaches (VNS and CC) to each other and each of those to the medication arm.

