#### Aim 1b

2.2.2

In a cross-sectional study across the 7 high-intensity sites, we will evaluate the two treatment pathways regarding expressive communication, behavior, and parent-reported quality of life of patients with validated diagnoses of LGS, and the impact of earlier (younger age) versus later (older age) utilization of the therapy. Caregivers will complete a series of surveys to assess their child’s communication, behavior, and quality of life.

#### Aim 2

2.2.3

In a retrospective cohort study across all 18 sites, we will analyze patterns of utilization of surgeries versus additional medication. We will also assess variation in their use across sites by age, race, ethnicity, health insurance, and overall medical complexity. Aim 2 will use the computable phenotypes for LGS that are developed from the intensive coding validation with EHR review and clinical diagnosis adjudication in the retrospective study cohort in Aim 1a.

Institutional Review Board (IRB) review for this protocol will be conducted at each study site, or in some cases via reliance upon a PEDSnet IRB protocol. All aspects of the study (Aims 1a, 1b, and 2) have received approval from the IRB of Ann & Robert H. Lurie Children’s Hospital. This study is registered at www.ClinicalTrials.gov (NCT05374824).

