#### Aim 1a

2.6.1

Agreement before and after consensus will be quantified with Cohen’s Kappa. The gold standard diagnosis of LGS will serve as the binary outcome variable, which is inclusive of either classic LGS or pragmatic LGS. We will develop computable phenotype models containing candidate factors available in EHR repository data (such as diagnosis codes, medications, and combinations thereof) that may discriminate between patients with and without LGS. We will compute the sensitivity, specificity, and the area under the curve. We anticipate identifying three computable phenotypes: one that optimizes sensitivity while maintaining acceptable specificity, one that optimizes specificity while maintaining acceptable sensitivity, and one that balances the two. Our goal is that this work would inform and could be applied in the selection of future study cohorts based on EHR or administrative data.

To test the computable phenotypes further, we will perform our primary analysis of ED and inpatient admissions with our gold standard definition of LGS and with each of the computable phenotype definitions. The computable phenotype that provides the least distortion from that measured using the gold standard may be used as the primary computable phenotype; however, we anticipate replicating all analyses with all computable phenotypes to account for the possibility that unanticipated multivariable interaction, or other issues perhaps related to data quality or completeness, may affect the results.

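### Phenotypes developed at 7 chart-reviewed sites alone define the Aim 2 cohort at 11 others, and the stated selection rule does not test whether case capture is accurate or stable between sites

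*Protocol article*

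**What the plan says.** Chart review and expert adjudication take place at the high-intensity sites only: "At 7 high-intensity sites, clinical research teams will conduct EHR review for coding validation of the diagnosis of LGS" (section 2.2). The phenotypes come from the same place: "Through a retrospective chart review study across the 7 high-intensity sites, we will validate" the LGS codes and build the phenotypes (section 2.2.1). The candidate predictors are items in the record "such as diagnosis codes, medications, and combinations thereof" (section 2.6.1).

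On performance, section 2.6.1 states: "We will compute the sensitivity, specificity, and the area under the curve". It expects three phenotypes, one favouring sensitivity, one favouring specificity and one balanced. As a further test, the analysis of ED visits and admissions is run under the adjudicated diagnosis and under each phenotype. Then: "The computable phenotype that provides the least distortion from that measured using the gold standard may be used as the primary computable phenotype". The same sentence adds that "we anticipate replicating all analyses with all computable phenotypes".

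For the remaining sites, section 2.2 says: "Data from an additional 11 sites (light-touch sites) will be pulled and analyzed based on cohort identification by these computable phenotypes". Table 1 gives the phenotype as the sole inclusion criterion for Aim 2. On what Aim 2 examines, section 2.2.3 says: "We will also assess variation in their use across sites by age, race, ethnicity, health insurance, and overall medical complexity". Section 2.6.3 summarises results by center among other factors, names chi-square or Fisher tests for categorical variables, and calls the comparisons exploratory.

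**The concern.** Aim 2 needs a phenotype that captures LGS accurately, and about equally well, at each site. The stated selection rule looks at something else: whether one outcome comparison, at sites where the adjudicated diagnosis exists, comes out close to the adjudicated result. Much the same patients enter both estimates, so they will agree in part by construction.

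The protocol itself gives reasons to expect uneven capture. Section 3.1 says that LGS is hard to diagnose accurately, that its definition has changed and that its features overlap with other severe epilepsies. A common data model standardises how data are stored, not how clinicians code. Because medications may enter the phenotype, case capture may also depend on one of the treatments whose use Aim 2 describes.

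At stake is the reading of Aim 2. If the proportion of true LGS among phenotype-positive patients differs by site, and the false positives have surgery less or more often than true cases, centers with identical practice will show different surgery shares. That could be read as variation in access or as disparity.

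**Working it through.** **How much of the cohort is affected.** Section 2.5 gives an average of over 200 LGS patients per high-intensity site and a total of more than 3,600 with the LGS code. 18 × 200 = 3,600 reproduces the total; 7 × 200 = 1,400 does not. If sites are of similar size, the 11 light-touch sites supply 11 × 200 = 2,200 of 3,600, or 61%.

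**What the selection rule can detect.** Suppose false positives have the same event rates as true cases within each treatment arm, but undergo surgery less often. The surgery-versus-medication rate ratio is then unchanged at any PPV, so the phenotype shows no distortion. The measured surgery share still moves with PPV. A phenotype can pass the stated test and still mislead Aim 2.

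**Size, as an illustration.** Inputs:
- s1, surgery share among true cases: 1/3. Section 2.5 expects this share in the surgery arm; that it holds at every site is an assumption made here.
- s0, surgery share among false positives: assumed.
- PPV by site: assumed.

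Measured share = PPV × s1 + (1 − PPV) × s0. The spread between two sites is therefore (difference in PPV) × (s1 − s0).

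| s0 | Site PPV | Measured share, low | Measured share, high |
|---|---|---|---|
| 10% | 60-90% | 0.6 × 1/3 + 0.4 × 0.10 = 24.0% | 0.9 × 1/3 + 0.1 × 0.10 = 31.0% |
| 5% | 60-90% | 0.6 × 1/3 + 0.4 × 0.05 = 22.0% | 0.9 × 1/3 + 0.1 × 0.05 = 30.5% |
| 20% | 60-90% | 0.6 × 1/3 + 0.4 × 0.20 = 28.0% | 0.9 × 1/3 + 0.1 × 0.20 = 32.0% |
| 10% | 50-95% | 0.5 × 1/3 + 0.5 × 0.10 = 21.7% | 0.95 × 1/3 + 0.05 × 0.10 = 32.2% |
| 1/3 | any | 33.3% | 33.3% |

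**What a test across centers would do.** A chi-square test over 18 sites was simulated with 200 patients per site, PPV evenly spaced over the range, 4,000 runs and a two-sided 5% level. True surgery use was identical everywhere. With PPV 60-90%, the test rejected in about 34% of runs at s0 = 10%, 54% at s0 = 5%, 11% at s0 = 20%, and close to the nominal 5% at s0 = 1/3. With PPV 50-95% and s0 = 10% it rejected in 77%.

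The calculation covers false positives only. Missed cases could act in the same way if capture differs by site and missed patients are treated differently from captured ones.

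**The case against.** A reader might infer that the phenotypes are built and scored on one pooled data set with no internal validation, and that coding differences will show up as treatment differences. The documents support neither. Section 2.6.1 does not say whether accuracy is apparent, cross-validated or by site, and an article may leave that to the full protocol or SAP. Distortion of Aim 2 needs two conditions together: accuracy that varies by site, and misclassified patients who are treated differently from true cases. The last row of the table shows it vanishing when the second fails.

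Other points stand in part:
- The selection rule is permissive, comes on top of sensitivity, specificity and AUC, and is followed by replication with every phenotype. That replication has value: if false positives drive site differences, the high-specificity phenotype should shrink them. It cannot reveal error that all three share, and all three come from the same 7 sites.
- The Aim 2 comparisons are exploratory, and center is one factor among several. This limits the consequence but does not remove it, since variation across sites is a stated purpose.
- The one-third figure follows directly on the Aim 1b sample size and may not describe surgery use in the Aim 2 cohort. It serves here only to set a scale.

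What the objection leaves untouched is the stated design itself: entry by phenotype alone at 11 sites, and a selection rule aimed at a different quantity from the one Aim 2 needs.

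**Conclusion.** The point holds in a limited form. As described, Aim 2 has no means of separating differences in coding from differences in treatment use at the 11 light-touch sites, and the rule for choosing the primary phenotype does not address this. The limitations in section 3.4 do not mention transfer of the phenotype to unreviewed sites.

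The size is unknown and may be zero. Under the assumptions above, spurious spread in surgery share is 7 percentage points at s0 = 10%, 4 points at s0 = 20% and none at s0 = 1/3, for a PPV range of 60-90%. The site PPVs and the surgery share among false positives are assumptions; nothing in the protocol fixes them. The Aim 1a results based on the adjudicated diagnosis at the 7 sites do not depend on this.

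**What to change.** 1. In the 7 reviewed sites, report sensitivity, specificity and PPV of each phenotype by site and with leave-one-site-out testing: build on six, test on the seventh, rotate. Charts without the LGS code are reviewed only as a sample (section 2.4.1), so weight by the sampling fractions.
2. Choose the primary phenotype for Aim 2 on held-out accuracy, not on closeness of the Aim 1a rate ratio. Keep the replication with all phenotypes.
3. Report Aim 2 for the 7 and the 11 sites separately as well as together.
4. Add a sensitivity analysis showing how much between-site variation the observed PPV range alone could produce, over a range of surgery shares among false positives that includes no difference from true cases.
5. List untested transfer to the 11 sites as a limitation.

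This takes wording and programming, with no data beyond those already planned. Reported accuracy may come out somewhat lower and site contrasts will be more cautious. Leave-one-site-out testing indicates how the phenotypes may perform at the 11 sites but does not measure it.

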**Figure 1 fig1:**
[figure not shown]
Map of sites. CRNs, clinical research networks; U, University.

The comparative effectiveness analyses will be conducted in populations selected in two ways: (1) patients with chart reviewed validated LGS diagnoses, and (2) patients with LGS based on computable phenotypes.

#### Aim 1a

2.2.1

Through a retrospective chart review study across the 7 high-intensity sites, we will validate the International Classification of Diseases, Tenth Revision (ICD-10) codes for LGS and will develop computable phenotypes for LGS.

In a retrospective cohort study across the 7 high-intensity sites, we will compare the effectiveness of epilepsy surgery versus additional medication for decreasing seizure-related ED visits and inpatient admissions in patients with validated diagnoses of LGS. This will entail a comparison of any surgery versus the medication arm, as well as comparisons of each of the two most common surgical approaches (VNS and CC) to each other and each of those to the medication arm.

#### Aim 1b

2.2.2

In a cross-sectional study across the 7 high-intensity sites, we will evaluate the two treatment pathways regarding expressive communication, behavior, and parent-reported quality of life of patients with validated diagnoses of LGS, and the impact of earlier (younger age) versus later (older age) utilization of the therapy. Caregivers will complete a series of surveys to assess their child’s communication, behavior, and quality of life.

#### Aim 2

2.2.3

In a retrospective cohort study across all 18 sites, we will analyze patterns of utilization of surgeries versus additional medication. We will also assess variation in their use across sites by age, race, ethnicity, health insurance, and overall medical complexity. Aim 2 will use the computable phenotypes for LGS that are developed from the intensive coding validation with EHR review and clinical diagnosis adjudication in the retrospective study cohort in Aim 1a.

Institutional Review Board (IRB) review for this protocol will be conducted at each study site, or in some cases via reliance upon a PEDSnet IRB protocol. All aspects of the study (Aims 1a, 1b, and 2) have received approval from the IRB of Ann & Robert H. Lurie Children’s Hospital. This study is registered at www.ClinicalTrials.gov (NCT05374824).

